## Abstract

**Background::**

Hashimoto thyroiditis (HT) is highly prevalent among reproductive-aged women and has a substantial negative impact on fertility. Currently, there is no specific treatment for Hashimoto thyroiditis. We hypothesize that acupuncture can halt or delay the progression of HT and improve fertility in child-bearing period female. We therefore designed a randomized controlled trial to test this hypothesis by comparing the therapeutic effect of acupuncture vs sham acupuncture in patients with Hashimoto thyroiditis.

**Methods::**

In this randomized controlled study, a total of 284 eligible patients will be assigned to acupuncture group (n = 142) or sham acupuncture group (n = 142) in a 1:1 ratio. All patients will receive 36 sessions in total for 12 consecutive weeks with the same acupoint prescription (RN23, ST9, RN17, RN4, RN6, ST36, SP6, KI6). The primary assessment is the titers of thyroid peroxidase antibodies (TPOAb) and thyroglobulin antibody (TGAb). Secondary outcomes include the thyroid function, ovarian function, the rate of primary ovarian insufficiency, and pregnancy outcome. The thyroid function and thyroid antibodies tests will be measured at weeks 0, 4, 8, and 12 after randomization. The ovarian function will be examined on the 2nd to 4th day of the menstrual period in the 1st month, 2nd month and 3rd month compared with baseline. Both the pregnancy outcome and the rate of primary ovarian insufficiency will be evaluated 1 year after treatment.

**Discussion::**

This will be the first large-scale trial specifically evaluating acupuncture therapy in child-bearing period female with Hashimoto thyroiditis. If the study confirms the effectiveness of acupuncture treatment, more consistent acupuncture therapy can be set up for clinical practice.

**Trial registration::**

Chinese Clinical Trials Register identifier, ChiCTR2000031320, registered on 27 March 2020.

## Introduction

1

Hashimoto thyroiditis (HT) known as autoimmune thyroiditis is a common autoimmune thyroid disease (AITD) and endocrine disorder.^[1–3]^ Surveys have shown that the prevalence of thyroid autoimmunity(TAI) and HT is 6% to 20%^[4]^ and 5% to 15%^[5]^ among reproductive-aged women, respectively. HT is characterized by increased levels of thyroid peroxidase antibodies (TPOAb) and thyroglobulin antibody (TGAb), diffuse lymphocytic infiltration of the thyroid gland, manifestations of goitrous or atrophic gland, and frequent thyroid dysfunction in varying degrees.^[6,7]^ HT is the most common cause of hypothyroidism.^[8]^ The pathogenesis is thought to be an immunologic attack that the presence of TPOAb tends to correlate with thyroidal damage and lymphocytic inflammation.^[9]^ TPOAb is directly cytotoxic to thyrocytes.^[10]^ In patients who have circulating thyroid peroxidase antibodies, there is a greater risk of progression from subclinical to overt hypothyroidism.^[11]^ A previous study indicates that largely increased levels of TPOAb are associated with a moderately increased risk of developing hypothyroidism in the patients of Hashimoto thyroiditis remained euthyroid.^[11]^ An epidemiological survey with a 20-year follow-up showed that the lifetime risk of incident hypothyroidism was 4% among TPOAb negative women, 23% for women with low-level TPOAb, 33% for those with mid-level TPOAb, and 53% for those with high TPOAb.^[12]^ Most cases of Hashimoto thyroiditis are considered to be the early stage of hypothyroidism. According to studies, 4% to 8% of the reproductive-age population suffered from subclinical hypothyroidism (SCH) with elevated thyroid stimulating hormone (TSH) more than 4.5 to 5.0 mIU/L and normal free thyroxine (FT4) levels concentration.^[13–15]^ The risk of progression from SCH to overt hypothyroidism (OH) ranges between 2% and 5% a year.^[12]^ It is well known that thyroid hormones play important roles during the development and maintenance of reproductive function in women.^[16]^ Numerous studies have suggested that thyroid autoimmunity and hypothyroidism associated with an adverse effect on fertility as well as pregnancy.^[4,17–21]^

For two decades, the association between TAI and reproductive failure has gained attention.^[17,22]^ Fertility is impaired in women with autoimmune thyroid disease.^[23]^ An extensive meta-analysis study reported that the presence of TPOAb combined with normal thyroid function was associated with an increased risk of unexplained subfertility, implantation failure, miscarriage, recurrent miscarriage, preterm birth, and maternal post-partum thyroiditis.^[24,25]^ A prospective study confirmed that the prevalence of TPOAb was greater (18%) in infertile women than that in healthy and fertile controls (8%).^[26]^ Autoimmune thyroid disorder and hypothyroidism have a negative impact on ovarian function.^[27,28]^ Women with AITD have lower serum anti-Müllerian hormone (AMH) levels compared with age-matched controls, which means women with AITD have prematurely aging ovaries.^[29]^ A prospective controlled trial revealed that 5% of patients of premature ovarian insufficiency (POI) presented highly elevated antithyroid antibodies.^[30]^ Besides, 24.1% of patients with premature ovarian failure (POF) had thyroid peroxidase autoantibodies.^[31]^ Idiopathic low ovarian reserve was associated with more frequent positive TPOAb in Chinese women.^[32]^ The human ovary is often the target of an autoimmune attack.^[33]^ In this context, HT is likely to be associated with ovarian dysfunction and diminished ovarian reserve. TPOAb has been detected in all samples of follicular fluid obtained from women with thyroid autoimmunity, while they were absent in women without thyroid autoimmunity. In these patients with HT, the levels of TPOAb in ovarian follicular fluid is positively correlated with serum antibody levels.^[34]^ Monteleone et al speculated that TPOAb might passed through the blood follicle barrier during follicular evolution and damage growing follicles and oocytes via thyroid hormone receptors on granulosa cells, which may result in decreasing the quality and development potential of oocyte.^[34]^ TPOAb targets TPO antigen on granulosa cells, creating a hostile local immune microenvironment around the oocyte.^[18]^ Subclinical or overt hypothyroidism is often caused by HT, which is associated with a diminished ovarian reserve in infertile patients of reproductive age.^[35,36]^ Recently, a retrospective study showed that SCH was associated with decreased ovarian reserve during later reproductive age.^[37]^ Therefore, Hashimoto thyroiditis has a substantial negative impact on the fecundity of reproductive-aged women. Impaired fertility has become a major public health problem that is associated with an increasing burden on society.

To date, there are no specific therapies to effectively reduce the autoantibody level of HT. Patients with HT who have normal thyroid function and no obvious symptoms of oppression should be followed up and monitored thyroid function regularly.^[38]^ Current therapeutic strategies for HT with normal thyroid function in the early stages include Se supplementation, glucocorticoids, and vitamin D.^[39–41]^ However, the available data on beneficial effects of Se on thyroid autoimmune parameters are limited.^[42]^ On the other hand, caution should be taken when long-term selenium supplementation, the increased risk of type 2 diabetes was observed in a randomized clinical trial.^[43]^ Only an ambiguous causal relationship and few interventional studies reported that Vitamin D is beneficial in the management of thyroid disease, so the therapeutic potential of vitamin D remains debated.^[41]^ Although some small trials appear promising of glucocorticoids, corticosteroid use has many negative effects on key aspects of early pregnancy.^[44,45]^ Once overt hypothyroidism is present, levothyroxine (LT4) is the treatment of choice for Hashimoto thyroiditis.^[9]^ Patients with HT who have the mere presence of detectable TPO antibodies does not, however, advocate empiric treatment with thyroid hormone.^[46]^ According to one study, women that are considered euthyroid, before pregnancy, are reclassified as having subclinical hypothyroidism, in cases of TSH between 2.5 and 4 mIU/L.^[47]^ Most endocrinologists use a TSH value of 2.5 mIU/L as the threshold for diagnosing hypothyroidism and starting levothyroxine in pregnant women because of an evident association between mild thyroid impairment and adverse outcomes in pregnancy.^[48]^ LT4 supplementation can slow the progression of HT, control the early stage of hypothyroidism, and support follicular development.^[49]^ The American Thyroid Association's recommendations for LT4 treatment also be considered for TPOAb positive women with normal thyroid function, although the quality of evidence is low.^[50]^ However, LT4 treatment before pregnancy in women is lacking sufficient data. An ideal TSH value before pregnancy can initiate a typical starting dose LT4 therapy (25–50 ug/d) When considering the potential benefits and risks minimization.^[50]^

According to the World Health Organization (WHO), acupuncture can be used to treat thyroid diseases. As integrative therapy or alternative medicine, acupuncture is safe and economical. Acupuncture can reduce symptoms and improve relevant biomarkers of thyroid disease patients.^[51]^ MOK pharmacopuncture ( a new form of acupuncture treatment) can regulate the imbalance of Th1/Th2 cytokines and help to suppress autoimmune response.^[52]^ Acupuncture can regulate the indexes related to immune function and correct the immune dysfunction to some extent, which is possibly the action mechanism of acupuncture-moxibustion in treating HT.^[53]^ Electroacupuncture (EA) intervention can regulate the thyroid hormone.^[54]^ The connection between thyroid and fertility is mainly based on cross-talk between the hypothalamic–pituitary–thyroid (HPT) axis and the hypothalamic–pituitary–gonadal (HPG) axis.^[16]^ The electroacupuncture has a benign regulating effect on the key hormones in the pituitary-target gland axis, such as thyroid-stimulating hormone (TSH), triiodothyronine (T3), tetraiodothyronine (T4), estradiol (E2), luteinizing hormone (LH) and follicle-stimulating hormone (FSH).^[55]^ Therefore, we can draw the preliminary conclusion that acupuncture can delay the progress of Hashimoto's thyroiditis and improve its fertility. Although acupuncture is increasingly used as a nonpharmacologic therapy in clinical practice, the level of available evidence is rated as “low”. We designed an RCT to evaluate the effects of acupuncture on halting or delaying the progression of HT and fertility improving in child-bearing period female.

## Methods and analysis

2

### Design

2.1

A single-center, patient-blinded, randomized controlled trial (RCT) is currently being performed. Acupuncture will be compared with sham acupuncture to determine if acupuncture has an effect on the reduction of antibody (TPOAb or TGAb) and fertility improving. The trial will be conducted in the Department of gynecology, Teaching Hospital of Chengdu University of Traditional Chinese Medicine. The protocol will be reported following the Consolidated Standards of Reporting Trials (CONSORT) statement and the Revised Standards for Reporting Interventions in Clinical Trials of Acupuncture (STRICTA).^[56,57]^ The flowchart of the trial is shown in Figure 1. The study schedule is detailed in Table 1. The Standard Protocol Items: Recommendations for Interventional Trials (SPIRIT) checklist is provided as Additional File 1.

**Figure 1 F1:**
[figure not shown]
Trial flow chart.

**Table 1 T1:**
[figure not shown]
Data collection points.

### Ethic approval

2.2

The research protocol is performed in accordance with the principles of the Declaration of Helsinki^[58]^ and has been approved by the Sichuan Regional Ethics Review Committee on Traditional Chinese Medicine (approval no. 2019KL-072). We registered the study on the Chinese Clinical Trial Registry (Registration No. ChiCTR2000031320).

### Inclusion criteria

2.4

Patients who meet all of the following conditions will be considered for enrollment. The inclusion criteria are as follows:

1.females, aged between 20 and 45 years;2.meet the diagnosis of HT with normal thyroid function(TSH<5.0 mIU/L) and is trying to conceive;3.willing to join this research and sign an informed consent form.

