### Sample size

2.6

Sample size will be decided by the primary outcome. The primary outcome of this study will be the mean change of TPOAb and TGAb from baseline to week 12. According to the results of our previous pilot study, titers of TPOAb was 253.86 ± 178.23 IU/ml in the acupuncture group and 318.98 ± 201.37IU/ml in the sham acupuncture group (TPOAb higher than 34IU/ml was the positive threshold of this research center). Considering participants recruited in the two groups are in a 1:1 ratio, the following formula was used to estimate sample size: 
[figure not shown]

With a 5% significance level (*α* = 0.05, two-sided) and 80% power (*β* = 0.2), at least 134 patients should be enrolled in each group and 284 total participants will be recruited to allow for a 10% dropout rate.

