### Statistical analysis

6.5

Statistical analyses of data will be performed using SPSS21.0 software (International Business Machines Corp., Armonk, NY) by professionals who will be blinded to the whole trial process. According to the principle of intention-to-treat (ITT), all randomized participants will be analyzed. Continuous variables with normal distribution will be expressed as Mean ± Standard Deviation (M ± SD) and compared by an independent sample Student *t* test. For abnormally distributed variables, they will be expressed as Medians ± Interquartile Range (MIQR) and nonparametric tests will be used. Categorical variables will be presented by frequency and percentage and analyzed by χ^2^ test or Fisher exact test. A repeated-measures multifactorial analysis will be used to analyze value changes of TPOAb, TGAb, fT3, fT4, TSH, thyroxine, AMH, FSH, LH, and E2 across 4 testing time points (See Table 1). The rest of the secondary outcomes will compare the proportions of patients with primary ovarian insufficiency and different pregnancy outcome. Safety analyses will be compared with the incidence of AEs in two groups using the χ^2^ test. Missing data will be handled by multiple imputation methods. All the tests will be two-sided, and a *P* value of less than .05 will be considered statistically significant.

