Thyroid peroxidase (TPO) and thyroglobulin(TG) are involved in thyroid autoimmunity as important antigens.^[65]^ TPO is the key enzyme in thyroid hormone synthesis.^[66]^ The thyroid hormones T3 and T4 are synthesized in the thyroid gland in a process that crucially involves the iodoglycoprotein thyroglobulin (TG).^[67]^ Antibodies against the main thyroid antigens (such as TPOAb and TGAb) can induce a chronic lymphocytic thyroiditis, eventually leading to the destruction and loss of thyroid function.^[21,68]^ TGAb may reflect a more initial type of immune response, while TPOAb can characterize later adaptive immune response, a sort of immune escalation. Positive TPOAb and/or positive TGAb, have been used test for screening for HT.^[69]^ TPOAb (positive in 95% of HT patients) as the best serological marker of HT is more sensitive than TGAb (positive in only 60%–80% of HT patients).^[7,70]^ Some surveys suggest that positive TPOAb are associated with an increased risk of developing hypothyroidism.^[11,12]^ In a cohort study, a TPOAb level above the threshold of 500 IU/ml was associated with a moderately increased risk for developing hypothyroidism.^[11]^ The presence of TPOAb negatively influences folliculogenesis, spermatogenesis, fertilization rates, embryo quality and pregnancy rates.^[71]^ In Chinese women, idiopathic low ovarian reserve is associated with more frequent positive TPOAb.^[32]^ Therefore, TPOAb and TGAb will be used as the primary outcome to assess the effect of acupuncture on delaying or preventing disease progression and improving fertility in child-bearing period female with HT. Except for thyroid antibodies, evaluation of thyroid function in patients with HT is carried out by measuring the serum levels of thyrotropin (TSH), free thyroxine (FT4), free triiodothyronine (FT3).^[7]^ Anti-Mullerian hormone (AMH) is secreted by the granulosa cells of growing ovarian follicles.^[72]^ AMH is a suitable biomarker of ovarian age in women of reproductive age and the most widely used and reliable serum biomarker of ovarian reserve.^[61,73]^ Follicle stimulating hormone (FSH) stimulates growth of ovarian follicles and aromatase expression in follicle granulosa cells. During reproductive aging in females, a rise in basal FSH is considered a sign of the reduction in the follicle reserve.^[74]^ Basal estradiol level is usually lower than 50pg/mL. It can indicate reproductive aging and hastened oocyte development if greater than 60 to 80 pg/mL in the early follicular phase.^[75]^ Luteinizing hormone (LH) plays an essential physiological role in follicle steroidogenesis and development and oocyte maturation. High basal LH levels are associated with significantly reduced fertilization rates and oocyte maturation, as well as impaired embryo quality, consequently resulting in an impaired pregnancy rate and higher miscarriage rate.^[76,77]^ Collectively, ovarian function will be assessed using the basal endocrine in the early follicular phase.

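### Pregnancy and live birth are compared without adjusting for age in women aged 20 to 45: the test is valid, but it gives up modest precision that would cost almost nothing to recover

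*Protocol article*

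**What the plan says.** All references are to the protocol article; no separate analysis plan is shown.

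- **Population** (2.4 Inclusion criteria): "females, aged between 20 and 45 years", with normal thyroid function and trying to conceive.
- **Randomisation** (2.7): stratified by TSH below 2.5 mIU/L against 2.5 to below 5 mIU/L. Age is not a stratum.
- **Outcomes** (6.2 Secondary outcomes): pregnancy rate, pregnancy losses, live birth rate and primary ovarian insufficiency, assessed at 6 months and 1 year after treatment. The ovarian hormones are listed separately and have a baseline measurement.
- **Analysis** (6.5 Statistical analysis): categorical variables go to a chi-square or Fisher exact test, and the secondary outcomes outside the repeated-measures analysis will "compare the proportions of patients with primary ovarian insufficiency and different pregnancy outcome". The hormones go into a repeated-measures multifactorial analysis whose factors are not listed. No covariate is named anywhere in the section.
- **Age and ovarian function** (7 Discussion): "AMH is a suitable biomarker of ovarian age in women of reproductive age". A rise in basal FSH is likewise described as a sign of shrinking follicle reserve during reproductive aging.
- **Sample size** (2.6): set on TPOAb titre alone, so the fertility outcomes played no part in choosing the number of women.

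**The concern.** Section 2.1 (Design) gives the trial two purposes, lowering antibodies and improving fertility. Pregnancy and live birth measure the second directly. Unlike a hormone level, they have no baseline value to adjust for, so any prognostic information has to come from other baseline variables. Across a 25-year age span, and given the article's own remarks on ovarian aging, age is an obvious candidate.

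A chi-square or Fisher test cannot carry a covariate. The stated method therefore rules age out, rather than leaving the question open. At stake is some precision on outcomes for which power was never planned, and an estimate that moves somewhat if the arms happen to differ in age. If no adjustment is named beforehand, a visible age difference may also prompt an adjustment chosen after the data are seen, which is hard to defend.

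**Working it through.** **1. The plan's own figure.** Inputs from section 2.6: "titers of TPOAb was 253.86 ± 178.23 IU/ml in the acupuncture group" and "318.98 ± 201.37IU/ml in the sham acupuncture group", two-sided alpha 0.05, power 80%.
- Difference = 318.98 − 253.86 = 65.12.
- Pooled SD = √[(178.23² + 201.37²)/2] = 190.15.
- n per arm = 2 × (1.960 + 0.842)² × 190.15² / 65.12² = 133.9, so 134.

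The stated 134 per arm reproduces, but it concerns TPOAb only. The steps below use the 142 per arm to be randomised.

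**2. Assumed inputs.** The article gives no pregnancy rate, age distribution or age effect. Assumed: 40% pregnant overall; age normal with mean 30 or 32 and SD 4 to 6, truncated to 20–45; log-odds of pregnancy falling by 0.05, 0.10 or 0.15 per year of age.

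**3. Variance explained by age.** R² = var{p(age)} / (0.4 × 0.6). Equivalent extra women = 284 × [1/(1 − R²) − 1].

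| Slope per year | R² | Equivalent extra women |
|---|---|---|
| 0.05 | 0.009 to 0.017 | 3 to 5 |
| 0.10 | 0.034 to 0.062 | 10 to 19 |
| 0.15 | 0.072 to 0.125 | 22 to 41 |

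At the top of the range: 284 × [1/(1 − 0.125) − 1] = 41.

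**4. Chance age imbalance.** SE of the difference in mean age = SD × √(2/142). After truncation the age SD is 3.91 to 5.37, which gives 0.46 to 0.64 years. The risk of pregnancy changes by about 1.2 points per year of age at slope 0.05, 2.3 at 0.10 and 3.2 to 3.3 at 0.15. A two-SE imbalance then moves the unadjusted risk difference by:
- low end: 2 × 0.46 × 1.19 = 1.1 points;
- high end: 2 × 0.64 × 3.15 = 4.0 points.

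**5. Compared with sampling error.** SE of the risk difference at 40% = √(2 × 0.24/142) = 5.8 points, a 95% half-width of 11.4 points. The shift in step 4 is therefore 1.1/5.8 = 0.2 to 4.0/5.8 = 0.7 of one SE, and an imbalance that large in either direction arises in about 1 trial in 20.

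**6. Power and type I error by simulation.** 4,000 trials per setting, 142 per arm, age mean 32 and SD 5, treatment odds ratio 2. Power is shown unadjusted, then age-adjusted.

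| Control rate | Age OR 0.8 per 5 years | 0.65 | 0.5 |
|---|---|---|---|
| 30% | 79.8% / 80.0% | 77.4% / 78.4% | 71.7% / 75.6% |
| 40% | 81.9% / 82.5% | 79.9% / 81.3% | 75.7% / 79.6% |

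The gain runs from about 0.3 to 4 percentage points. With no treatment effect, the unadjusted test rejects in 4.4% to 5.1% of trials.

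**7. Hormones, for contrast.** Assume a correlation with age of 0.3 to 0.5 and a baseline-to-follow-up correlation of 0.7 to 0.9. Once the baseline value is in the model, adding age is worth only about 0.5% to 6% of the sample.

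**The case against.** **Covariate lists belong in the analysis plan.** The plan is not shown, and a journal article condenses the full protocol. This would settle the matter if the article were silent on method. It is not: it names a test that cannot take a covariate, so a plan that adjusts for age would have to replace that test. The objection does stand to this extent: an unadjusted comparison of secondary proportions in a randomised trial is not an error, and replacing it is an improvement.

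**The unadjusted result is not biased.** A reader might infer that a chance age difference invalidates the comparison. It does not. Randomisation protects the test, chance imbalance is already reflected in its standard error, and the simulated type I error stays near 5%. The shift in step 4 describes an unlucky draw.

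**The hormone analyses are not shown to ignore age.** A reader might extend the point to AMH, FSH, LH and E2. Section 6.5 does not list the factors of that model, so the absence of age cannot be read from it. Each woman's baseline value also carries most of the age effect (step 7).

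**The size is assumed.** This stands. With a weak age slope the gain is only 1% to 2%. The article links AMH and FSH to ovarian aging but gives no effect of age on pregnancy, and baseline AMH and FSH would also be available as predictors.

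**Conclusion.** The point holds for pregnancy and live birth. The stated analysis is valid but leaves out a baseline variable that is already known and plausibly prognostic. Under the assumptions in step 2, the loss is about 1% to 13% of outcome variance, and a two-SE chance age imbalance would move the risk difference by about 1 to 4 points. Simulated power gains are about 0.3 to 4 points, with the upper end requiring the odds of pregnancy to halve every five years of age. The direction is secure, since adjustment did not lower power in any setting tried. The size is not, because it depends on a pregnancy rate, an age distribution and an age effect that the article does not give. This is a worthwhile, low-cost improvement to secondary analyses. It does not bear on the validity of the trial or on the primary outcome, and it does not extend to the hormone models.

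**What to change.** For pregnancy and live birth, prespecify logistic regression with treatment arm, age at randomisation as a continuous term, and TSH stratum. From that model, report the standardised risk difference with a 95% CI. This keeps the result on the scale of a difference in proportions, as the article intends. Keep the chi-square or Fisher test as a supportive analysis. Leave ovarian insufficiency, and any other outcome with few events, as an unadjusted comparison. If an analysis plan already names such a model, bring section 6.5 into line with it.

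The cost is one covariate named before unblinding, plus some programming for the standardisation. No new data are needed, because age is established at eligibility and TSH stratum at randomisation.
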